### Intention-to-treat

Analysis of all patients will be performed according to the intention-to-treat principle. However, data will also be presented per-protocol and for the actual treatment groups. This especially concerns converted laparoscopic operations, where patients will cross over to the open group. We consider it important to present also the actual treatment data, as they will be useful especially for systematic reviewers.

## Discussion

### Justification of the trial

Currently only low-level evidence supports the implementation of laparoscopic liver resection over open liver resection for the surgical management of hepatic colorectal metastases. Thus, the trial is scientifically and ethically justified.

### Selection of endpoints

The primary endpoint of this study is complications within 30 days, reported using the Accordion system [25] and the Comprehensive Complication Index [27]. Serious complications after surgery have been shown to influence survival for several surgical treatments, including liver resection for colorectal metastases [17], gastric resection for cancer [49] and pancreatoduodenectomy for periampullary cancer [50]. However, complication data on atypical liver resections are not easily available, as most reported material on open liver resections includes formal and extended resections as well as atypical resections. Thus a moderate 27% expected complication rate for open resections [17,19,48] and 13% for laparoscopic resections was chosen [19,47,51,52]. In the years prior to the study, most atypical liver resections in our hospital were performed by laparoscopy, and currently more than 600 laparoscopic major and minor liver resections have been performed at Oslo University Hospital.

### Enhanced recovery after surgery

The optimization of perioperative care has received much attention over the last two decades. ERAS protocols aim to attenuate stress response, thus reducing complications, length of stay and improving patient comfort. An ERAS protocol, which has strict guidelines for oral intake, use of analgesics and early mobilization, ensures similar treatment of both groups in a surgical randomized controlled trial. This will improve the trial quality not only by enhancing recovery in both groups, but by improving the performance of the control group. The Orange II trial also follows an ERAS protocol [36].

### Single center versus multicenter

The Oslo-CoMet study is a single center study from a high volume Hepato Pancreato Biliary (HPB) laparoscopy center. After the merger of hospitals in Oslo, our HPB centre has solitary treatment responsibility for the 2.8 million people in the South-Eastern Norway Regional Health Authority [53]. This allowed to us create one algorithm for radiology, recruitment, surgical technique, chemotherapy and follow-up. These advantages, together with the lack of possible partners (there are no comparable laparoscopic HPB centers in the Nordic countries), helped the study group decide that a single center study was most suitable.

The Intervention Centre at Oslo University Hospital is a research and development unit with long experience in development and implementation of surgical procedures. The centre has a framework well suited for running a randomized controlled trial. The study is a joint venture between the Department of HPB Surgery, Oslo University Hospital, and the Intervention Centre, with direct funding from the South-Eastern Norway Regional Health Authority.

### Choice of resections

The study will include all liver resections less than three segments, atypical and anatomical. Thus, there will be a great diversity of operations included, from small wedge resections to large parenchyma sparing resections. The randomization is expected to equalize these differences. This design closely reflects the reality of todays parenchyma sparing treatment of colorectal liver metastases [54,55]. The Orange II plus trial, a multicenter trial of laparoscopic versus open hemihepatectomy, is currently recruiting patients and will supplement the scientific picture with results of formal hepatectomies. The Oslo-CoMet trial will also verify the safety and effect of parenchyma sparing liver resections for colorectal liver metastases.

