## Background

Colorectal cancer is the third most common cancer worldwide [1]. In 2008 it accounted for 608,700 deaths globally, most of whom died of metastatic tumors [1]. Surgical resection is currently considered the only curative treatment for colorectal liver metastases, with 5-year survival rates following resection between 30% and 58% [2-5].

There are two surgical approaches to resection of liver tumors - open and laparoscopic. No randomized controlled trial comparing the two methods has been completed, but cohort and case-matched studies found a significantly reduced length of hospital stay and need for postoperative opiates after laparoscopic liver resection [6-8]. Long-term oncologic outcomes for laparoscopic liver resection are comparable to open liver resection in retrospective studies [9-11], and meta-analyses of observational studies support these findings [12-14].

Postoperative morbidity after surgery is a major cause of patient suffering and societal costs. The incidence of postoperative morbidity in observational studies on patients undergoing open liver surgery varies from 22% to 47% [15-17], whereas for laparoscopic resection the morbidity rate varies from 11% to 15% [18-20]. Laparoscopic liver resection in patients who previously have undergone open liver resection has a morbidity rate of 29% [21].

In October 2014, the 2^nd^ International Consensus Conference on Laparoscopic Liver Resection was held in Morioka, Japan [22]. At this consensus conference, laparoscopic liver resection was still judged to be in the assessment phase (Balliol grade 3 [23]), as the all the existing evidence is of low quality. The jury recommended that higher quality studies should be performed, using standardized reporting of 90 days mortality and complication rates (article in press, *Annals of Surgery*).

The aim of this randomized controlled trial will thus be to determine whether laparoscopic liver resection of colorectal liver metastases results in less postoperative morbidity than open liver resection.

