### Statistics

After reviewing our own data and the literature, we expect a 13% morbidity rate in the laparoscopic group [19,47] and a 27% rate in the open group [17,19,48]. With a significance level of 5% and two-sided test, 254 patients will be needed to complete the study with 80% power. To allow for 10% dropout, we plan to include 280 patients.

Descriptive statistics will be used to describe baseline data. We will use statistical methods for contingency tables and categorical data to analyze rates and proportions at single time points. Statistical analyses for repeated measures will be used to investigate developments over time. To assess mortality, survival analysis will be performed.

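### Naming a few pre-randomisation covariates for the 30-day morbidity comparison, and adjusting SF-36 for baseline, would be a cheap improvement to a valid plan

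*Protocol article*

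**What the plan says.** Under Statistics the article gives one sentence on the analysis of rates: "We will use statistical methods for contingency tables and categorical data to analyze rates and proportions at single time points". It names no covariate. The sample size rests on a comparison of two proportions: "we expect a 13% morbidity rate in the laparoscopic group" and "a 27% rate in the open group", and then "With a significance level of 5% and two-sided test, 254 patients will be needed to complete the study with 80% power".

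Under Choice of resections the article says that operations will range from small wedges to large parenchyma-sparing resections. The only safeguard it gives is "The randomization is expected to equalize these differences". The Randomization procedure section gives a 2:1:1 ratio, which is 1:1 for laparoscopic against open. It names no stratification factor and says that details can be had on request.

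The Background supplies one prognostic contrast. Laparoscopic morbidity is put at 11% to 15%, but laparoscopic resection after an earlier open liver resection "has a morbidity rate of 29" per cent. The eligibility section excludes previous ablation, not previous resection. All patients have CT and MRI before inclusion (Study design), and tumours are numbered by size before surgery (Resection margins).

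SF-36 is collected at baseline, 30 days, 4 months and 24 months. The stated analysis is "Statistical analyses for repeated measures will be used to investigate developments over time".

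**The concern.** Randomisation balances prognostic factors on average over repeated trials. It does not guarantee balance in one trial of 254 patients. Here the article calls the case mix diverse, cites a factor that may double morbidity, and obtains relevant data before surgery, yet the stated analysis makes no use of them.

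Two things are at stake, both modest. One is a small gain in power that needs no further patients. The other is the credibility of the single result: if a visible imbalance turns up, covariates chosen afterwards would look data-driven, in a trial whose patients and surgeons are not blinded. For SF-36 the same reasoning applies to the baseline score, which is usually the strongest predictor of later scores.

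**Working it through.** **1. Reproduce the plan's figure.** Inputs from Statistics: 13% and 27%, two-sided 5%, 80% power, equal arms. Pooled-variance formula without continuity correction:

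n per arm = [1.960·√(2·0.20·0.80) + 0.842·√(0.27·0.73 + 0.13·0.87)]² / 0.14² = [1.109 + 0.469]² / 0.0196 = 126.96, rounded up to 127.

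The total is 254, an exact match, and power at 127 per arm is 0.800. The stated 80% therefore already belongs to the crude comparison.

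**2. Indicative size of the prognostic factor.** From 29% (Background) and 13% (the planning rate in Statistics): (0.29/0.71)/(0.13/0.87) = 0.4085/0.1494 = 2.73. The two rates come from different sources, and the 29% concerns laparoscopic surgery only, so applying 2.73 to both arms is an assumption. The article gives no prevalence; 10% to 30% is assumed.

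**3. Power with adjustment.** Simulation with 127 per arm, marginal rates held at 13% and 27%, 10,000 runs. It compares the crude pooled z-test with a likelihood-ratio test for arm in a logistic model containing the factor.

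| Assumed prevalence | Crude | Adjusted | Gain (points) |
|---|---|---|---|
| 10% | 0.799 | 0.815 | 1.5 |
| 20% | 0.804 | 0.819 | 1.5 |
| 30% | 0.801 | 0.824 | 2.3 |

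With an assumed continuous prognostic score instead (6,000 runs), adjusted power was 0.81 at an AUC of 0.58, 0.82 at 0.64 and 0.68, 0.86 at 0.75 and 0.89 at 0.79. A gain near 9 points thus needs a far stronger predictor than any the article quantifies. In the null runs of that second set, type I error was 4.5–5.0% crude and 5.1–5.4% adjusted, so a small part of the gain may come from a slightly more liberal test.

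**4. Chance imbalance.** If allocation is simple (an assumption), the SD of the between-arm difference in prevalence q is √(2q(1−q)/127). At q = 0.20 this is √(0.32/127) = 0.050. The probability of an imbalance above 10 points is 4.6% at q = 0.20, 8.2% at 0.30 and 11.1% at 0.50.

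**5. Effect of a 10-point imbalance.** At 20% prevalence and odds ratio 2.73:
- Open arm: risks of 22.6% without and 44.4% with the factor average to 27% (0.8·22.6 + 0.2·44.4). The contrast is 21.8 points, and 0.10·21.8 = 2.2.
- Laparoscopic arm: risks of 10.3% and 23.9% average to 13%. The contrast is 13.6 points, and 0.10·13.6 = 1.4.
- If the imbalance is shared between the arms, the shift is (2.2 + 1.4)/2 = 1.8.

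That is about 2 points against a planned difference of 14.

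**6. Feasibility.** Expected events: 127·0.13 + 127·0.27 = 16.5 + 34.3, about 51. Arm plus three covariates is four coefficients, or about 13 events each (51/4), which a logistic model can carry.

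**7. SF-36.** If the repeated-measures contrast is in effect a change score, its variance relative to a baseline-adjusted one is 2/(1+ρ): 1.54, 1.33 and 1.18 at assumed correlations of 0.3, 0.5 and 0.7. The article specifies neither form of contrast.

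**The case against.** The strongest reply is that nothing here is wrong. A crude comparison of two randomised proportions, in a trial sized for that comparison, is valid. That stands in full.

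A reader might infer three stronger things, and the document supports none of them.
- *That the primary analysis is fixed as unadjusted.* The article never says so. Categorical-data methods can include Mantel–Haenszel or logistic regression, and a covariate list is commonly left to the statistical analysis plan, which is not at hand.
- *That balance is left to simple chance.* Stratification is neither stated nor excluded, because the randomisation details are held elsewhere. The imbalance probabilities above therefore hold only if allocation is simple.
- *That power is lost or the comparison biased.* The 80% is delivered. Chance imbalance does not bias a randomised comparison on average or inflate its type I error, and the crude standard error already allows for it.

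It is also fair to say that the plan has some margin: "To allow for 10% dropout, we plan to include 280 patients". With no dropout at all, 140 per arm would give the crude test about 84% power, more than adjustment adds at 254.

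Finally, the article does not show that every candidate covariate is recorded before randomisation. Imaging precedes inclusion, but tumour numbering is only said to precede surgery, and planned extent could be settled after allocation. This limits the list of covariates; it does not remove the case for one.

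**Conclusion.** The point holds as a low-cost improvement, not as an error. The article relies on randomisation for a case mix that it calls diverse and names no covariate, although useful pre-operative information is obtained anyway. For the one factor it allows to be quantified, prespecified adjustment is worth about 1.5 to 2.3 points of power. It would also account for a shift of about 2 points if a 10-point imbalance arose.

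These sizes rest on an indicative odds ratio of 2.73 from separate sources, applied to both arms, and on assumed prevalences of 10–30%. The SF-36 gain is likely real, but its size depends wholly on a correlation that the article does not give.

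**What to change.** Before outcomes are tabulated by arm, state in the statistics section or the analysis plan:

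- **Primary analysis:** a logistic model for 30-day morbidity with arm (laparoscopic or open), previous liver resection, and number and largest size of metastases taken from the pre-inclusion imaging. Add planned extent only if it was recorded before allocation. If the randomisation details show stratification, include those factors too.
- **Reporting:** the standardised risk difference with 95% CI, with the accompanying test named in advance. Keep the contingency-table result as supportive.
- **SF-36:** in the repeated-measures model, enter the baseline score as a covariate or constrain the arms' baseline means to be equal.

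The timing allows it. Trial status reports 200 patients included by 10 January 2015, no interim analysis planned, and primary results withheld until recruitment is complete. The SF-36 wording is the more urgent part, because first quality-of-life results are due once 120 patients reach 4 months.

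The cost is wording, a slightly more complex primary analysis, and a check that previous resection and tumour size are recorded from the pre-operative work-up. No extra patients or visits are needed.

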### Blinding

Blinding of patients for a surgical procedure can be performed using large wound dressings, but the epidural analgesia will be almost impossible to hide. We found that adequate blinding of surgeons and nursing personnel would be virtually impossible in our department. The reason for blinding of patients is primarily to avoid the change of behavior in the trial [56]. As the patients are informed about randomization only the evening before surgery, we judge that possibility for change of behavior is small. The primary endpoint is morbidity, an objective parameter that the patient cannot influence. We admit, though, that the reporting of pain, quality of life and to a certain degree the length of stay could be influenced by the fact that the patients know which operation they have had.

We still realize that lack of blinding may weaken the study. Patients receiving their preferred treatment may perform better than they otherwise would have, and *vice versa*. Our experience is, however, that some patients will prefer the “safe” option of open surgery while others will prefer the “modern” laparoscopic surgery.

## Trial status

As of 10 January 2015, 200 patients have been included in the Oslo-CoMet study. The samples for the first immunology study have been analyzed and results will be published shortly. The first quality of life data will be published when 4 months follow-up of the first 120 patients is ready. Tissue from the bio bank is being processed and more than 50 samples have been analyzed using the Ion Torrent® platform (Life Technologies, Grand Island, NY, USA). Data concerning primary and secondary endpoints will not be published until the expected number of patients is reached. No interim analysis is planned but safety issues are continuously evaluated.

The Oslo-CoMet study (NCT01516710) will to our knowledge be the largest randomized controlled trial on laparoscopic versus open resection of colorectal liver metastases. The Orange II (NCT00874224) and Orange II plus (NCT01441856) trials are currently recruiting. A Chinese (NCT01768741) and a South Korean (NCT00606385) trial of hepatocellular carcinoma resections are also recruiting patients. Together these trials will provide level 1 evidence on the comparison of open and laparoscopic liver surgery. The Oslo-CoMet study is planned to complete recruitment in 2015.

## Abbreviations

CONSORT: Consolidated Standards of Reporting Trials
CRF: case report form
CT: computed tomography
DSMB: Data and Safety Management Board
ERAS: enhanced recovery after surgery
HPB: Hepato Pancreato Biliary
PCA: patient-controlled analgesic pump
SF-36: short-form 36-item
